## 【Summary of Clinical Study Protocol】

|                                  |                                                                                                                                                                                                                                                                                                                                                                                                                                                                                                                                                                                                                                                                                                                                                                                                                                                                                                    |
|----------------------------------|----------------------------------------------------------------------------------------------------------------------------------------------------------------------------------------------------------------------------------------------------------------------------------------------------------------------------------------------------------------------------------------------------------------------------------------------------------------------------------------------------------------------------------------------------------------------------------------------------------------------------------------------------------------------------------------------------------------------------------------------------------------------------------------------------------------------------------------------------------------------------------------------------|
| Title                            | Double-blind, Multi-center randomized, prospective confirmatory clinical study to evaluate the efficacy and safety of MegaShield using for anti-adhesion after total thyroidectomy                                                                                                                                                                                                                                                                                                                                                                                                                                                                                                                                                                                                                                                                                                                 |
| Purpose                          | The purpose of this study is to evaluate the anti-adhesion effect of MegaShield after thyroidectomy by applying MegaShield or Guardix-SG to patients who have undergone total thyroidectomy to compare anti-adhesion effect and safety.                                                                                                                                                                                                                                                                                                                                                                                                                                                                                                                                                                                                                                                            |

| Study Period                     | 32 months from the date of approval (April 2018 ~ December 2020)                                                                                                                                                                                                                                                                                                                                                                                                                                                                                                                                                                                                                                                                                                                                                                                                                                   |
| Number of Subjects               | 140 subjects (70 in each of the test group and the control group)                                                                                                                                                                                                                                                                                                                                                                                                                                                                                                                                                                                                                                                                                                                                                                                                                                  |
| Investigational Device           | 
 
· Experimental : MegaShield: A transparent or milky gel-type liquid manufactured by mixing acellular dermal matrix powder, cross-linked hyaluronic acid and thermo-sensitive polymer(poloxamer)
 
· Comparator : Guardix-SG: A product consisting of poloxamer and sodium alginate
 
                                                                                                                                                                                                                                                                                                                                                                                                                                                                                                                                                        |
| Inclusion and Exclusion Criteria | 
<Inclusion Criteria>
 
Subjects who meet all of the following criteria shall participate in the clinical trial:
 
 
1) a patient who gives written informed consent spontaneously;
 
2) a patient who is between 20 and 70 years of age;
 
3) a patient who can participate the clinical trial during the entire study period;
 
4) a patient who is required total thyroidectomy due to thyroid disease;
 
5) a patient who are scheduled to undergo thyroidectomy for the first time related to thyroid disease;
 
6) a patient with no liver dysfunction, anemia or renal inadequacy in preoperative testing; and
 
7) a patient who agreed to contraception while participating in the clinical trial after application of investigational device.
 
 
<Exclusion Criteria>
 |

|                                |                                                                                                                                                                                                                                                                                                                                                                                                                                                                                                                                                                                                                                                                                                                                                                                                                                                                                                                                                                                                                                                           |
|--------------------------------|-----------------------------------------------------------------------------------------------------------------------------------------------------------------------------------------------------------------------------------------------------------------------------------------------------------------------------------------------------------------------------------------------------------------------------------------------------------------------------------------------------------------------------------------------------------------------------------------------------------------------------------------------------------------------------------------------------------------------------------------------------------------------------------------------------------------------------------------------------------------------------------------------------------------------------------------------------------------------------------------------------------------------------------------------------------|
|                                | 
Subjects who fall under any of the following criteria shall be excluded from the clinical trial:
 
 
1) a pregnant or breast-feeding female patient; or a female who plans to become pregnant within 1 month after applying the investigational device;
 
2) a patient with serious liver or kidney disease;
 
3) a patient with lymphatic or hemostatic disorders; or a patient taking an anticoagulant;
 
4) a patient who receives an oral or a parenteral hypoglycemic agent for diabetes;
 
5) a patient immunosuppressed; or a patient with autoimmune diseases;
 
6) a patient with serious systemic disease;
 
7) a patient scheduled for accompanied follow-up surgery;
 
8) a patient undergoing chemotherapy for a cancer other than thyroid cancer;
 
9) a patient who is treated by another anti-adhesion; or
 
10) a patient deemed inappropriate for this study by the investigator (including non-cooperative, etc.).
 
 |
| Study Procedure                | 
Assign patients who meet the inclusion/exclusion criteria according to the randomization table. Perform total thyroidectomy on subjects on the day of surgery, and apply the assigned medical device. When applying the investigational products, apply 5 ml of MegaShield for the test group and 5 ml of Guardix-SG for the control group on the surface of the thyroidectomy area and the strap muscle. Evaluate the efficacy and safety at the visits 1 week and 6 weeks after surgery.
                                                                                                                                                                                                                                                                                                                                                                                                                                                                                                                                                         |
| Evaluation Method and Criteria | 
Efficacy Evaluation
 
 
· Primary efficacy endpoint : Compare the esophageal movement between the two groups using marshmallow esophagography at 6 weeks after surgery to evaluate the severity of adhesion.
 
· Secondary efficacy endpoint : Compare the Adhesion Scores between the two groups at screening, 1 week and 6 weeks after surgery.
 
 
Safety Evaluation
 
Collect all adverse events : At every visit after surgery
                                                                                                                                                                                                                                                                                                                                                                                                                                                                                                                       |
| Statistics                     | 
The main analysis is the mITT set, and the PP set is additionally analyzed. The analysis for the safety is ITT set.
 
 
· ITT Set: An analysis set targeting for subjects who have received treatment at least once with an investigational product, among all
 
                                                                                                                                                                                                                                                                                                                                                                                                                                                                                                                                                                                                                                                                                                                                       |

|  |                                                                                                                                                                                                                                                                                                                                                                                                                                                                                                                                                                                                                                                                                                                                                                                                                                                                                                                                                                                                                                                                                                                                                                                                                                                                                                                                                                                                                                                                                                                                                                                                                                   |
|--|-----------------------------------------------------------------------------------------------------------------------------------------------------------------------------------------------------------------------------------------------------------------------------------------------------------------------------------------------------------------------------------------------------------------------------------------------------------------------------------------------------------------------------------------------------------------------------------------------------------------------------------------------------------------------------------------------------------------------------------------------------------------------------------------------------------------------------------------------------------------------------------------------------------------------------------------------------------------------------------------------------------------------------------------------------------------------------------------------------------------------------------------------------------------------------------------------------------------------------------------------------------------------------------------------------------------------------------------------------------------------------------------------------------------------------------------------------------------------------------------------------------------------------------------------------------------------------------------------------------------------------------|
|  | 
subjects enrolled in this clinical trial
 
 
· Modified ITT Set: An analysis targeting for subjects who have received treatment at least once with an investigational product and participated in the primary efficacy endpoint evaluation, among all subjects enrolled in this clinical trial
 
· PP set: An analysis targeting for subjects who completed the study in accordance with this protocol without any significant violation of the protocol among ITT set
 
 
The primary endpoint is evaluated by providing the frequency, proportion, mean, standard deviation, median, minimum and maximum of the esophageal movement scores and by using the one-sided 97.5% confidence interval for the difference in the mean score of the 'esophageal movement' between the two groups to determine whether the effect of the new treatment is non-inferior to the existing treatment.
 
The secondary endpoint is evaluated by providing descriptive statistics (mean, standard deviation, median, minimum and maximum) by time point and group, and by providing descriptive statistics of the mean changes, compared to those at the screening, for each time point and each group after surgery.
 
The safety is analyzed on the ITT set. For all adverse events reported in the study period, the number of subjects with adverse events, the proportion, and the number of cases shall be calculated by group. The incidence of adverse events in the test group and control group shall be analyzed by chi-square test (Fisher's exact test).
 |
|--|-----------------------------------------------------------------------------------------------------------------------------------------------------------------------------------------------------------------------------------------------------------------------------------------------------------------------------------------------------------------------------------------------------------------------------------------------------------------------------------------------------------------------------------------------------------------------------------------------------------------------------------------------------------------------------------------------------------------------------------------------------------------------------------------------------------------------------------------------------------------------------------------------------------------------------------------------------------------------------------------------------------------------------------------------------------------------------------------------------------------------------------------------------------------------------------------------------------------------------------------------------------------------------------------------------------------------------------------------------------------------------------------------------------------------------------------------------------------------------------------------------------------------------------------------------------------------------------------------------------------------------------|

## 【Schedule of Clinical Study】

| Item                                         | Screening | Application and Evaluation |         |          |
|----------------------------------------------|-----------|----------------------------|---------|----------|
| Visit                                        | Visit 1   | Visit 2                    | Visit 3 | Visit 4  |
| Day                                          | -30~0     | Day 0                      | Day 7±3 | Day 42±7 |
| Written consent                              | ●         |                            |         |          |
| Inclusion/exclusion criteria                 | ●         |                            |         |          |
| Demographic survey/physical examination      | ●         |                            |         |          |
| Vital signs test                             | ●         |                            |         | ●        |
| Medical/administering history  | ●         |                            |         |          |
| Subjects enrollment                          |           | ●                          |         |          |
| Surgery and applying investigational product |           | ●                          |         |          |
| Esophagography                               |           |                            |         | ●        |
| Evaluating adhesion scores                   | ●         |                            | ●       | ●        |
| Urine β-HCG testing (for fertile women)      | ●         |                            |         | ●        |
| Hematological test                           | ●         |                            | ●       | ●        |
| Serum biochemical test                       | ●         |                            | ●       | ●        |
| Urinalysis                                   | ●         |                            | ●       | ●        |
| Collecting concomitant drug    | ●         | ●                          | ●       | ●        |
| Collecting adverse event       |           | ● (After surgery)          | ●       | ●        |

(1) Collect medical history within 5 years before participating in the clinical trial.

(2) Collect information on drugs that have been administered within 4 weeks of the screening visit or are currently being administered.

(3) Adverse events should be followed up until the symptoms disappear, and if it is difficult for a subject to visit, the follow-up should be performed by phone. (However, if a subject is diagnosed with hypothyroidism or hypoparathyroidism through thyroid function test after thyroidectomy, the resulting adverse events should be followed up until the last visit of the subject for the clinical trial.)

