(3) Adverse events should be followed up until the symptoms disappear, and if it is difficult for a subject to visit, the follow-up should be performed by phone. (However, if a subject is diagnosed with hypothyroidism or hypoparathyroidism through thyroid function test after thyroidectomy, the resulting adverse events should be followed up until the last visit of the subject for the clinical trial.)

Receive informed consent to participate in the clinical trial from patients who are judged to be in need of total thyroidectomy. After checking the results of hematological test, serum biochemical test and urinalysis, and the inclusion/exclusion criteria, assign a subject identification code only to subjects judged to meet the criteria. In addition, give subjects the randomization number (3 digits) in order according to the randomization table and assign the subjects to the appropriate application group. The randomization code and the subject identification code will be used as the subject number during the clinical trial. The target patient shall have total thyroidectomy and then be subject to the assigned investigational product. When applying the investigational product, apply 5 ml of MegaShield and 5 ml of Guardix-SG for the test group and the control group, respectively, on the thyroidectomy site and the surface of strap muscles. Visit the 1st and 6th weeks after surgery to evaluate the efficacy and safety.

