## **11.1. Observation and clinical testing items**

### 1) Visit 1 : Screening (Day -30~0)

Subjects who have agreed to participate in this clinical trial should be screened to ensure that they are eligible to participate in the study.

- Receive informed consent
- Review inclusion/exclusion criteria
- Demographic survey/physical examination : Date of birth, gender, weight, height, etc.
- Vital signs test : Blood pressure, pulse rate
- Medical/administering history : Diabetes mellitus, hypertension, stroke, ischemic heart disease, malignant tumor, acute infection, allergy, and whether taken bisphosphonate, etc.
- Evaluate adhesion scores
- Urine  $\beta$ -HCG testing (only for women with childbearing age)
- Hematological test : RBC, Hemoglobin, Hematocrit, Platelet, WBCs, Neutrophil, Lymphocyte, Monocyte, Eosinophil, Basophil, Blood coagulating time (PT/APTT)
- Serum biochemical test : sodium, Potassium, Chloride, Creatinine, BUN, ALT, AST,ALP, Total Bilirubin, Albumin, Total Protein, Total Cholesterol, Glucose
- Urinalysis : pH, Specific gravity, WBC, Protein, Bilirubin, Glucose, Urobilinogen, Ketone, Nitrite, Blood
- Collect concomitant drugs

### 2) Visit 2 : Day 0

- Perform a surgery and apply an investigational product
- Enroll subjects
- Collect concomitant drugs
- Collect adverse events : After surgery

### 3) Visit 3 : Day 7 $\pm$ 3

- Evaluate adhesion scores
- Hematological test : RBC, Hemoglobin, Hematocrit, Platelet, WBCs, Neutrophil, Lymphocyte, Monocyte, Eosinophil, Basophil, Blood coagulating time (PT/APTT)
- Serum biochemical test : sodium, Potassium, Chloride, Creatinine, BUN, ALT, AST,ALP, Total Bilirubin, Albumin, Total Protein, Total Cholesterol, Glucose
- Urinalysis : pH, Specific gravity, WBC, Protein, Bilirubin, Glucose, Urobilinogen, Ketone, Nitrite,

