#### 4) Visit 4 : Day 42±7

- Check vital signs
- Esophagography
- Evaluate adhesion scores
- Urine β-HCG testing (only for women with childbearing age)
- Hematological test : RBC, Hemoglobin, Hematocrit, Platelet, WBCs, Neutrophil, Lymphocyte, Monocyte, Eosinophil, Basophil, Blood coagulating time (PT/APTT)
- Serum biochemical test : sodium, Potassium, Chloride, Creatinine, BUN, ALT, AST,ALP, Total Bilirubin, Albumin, Total Protein, Total Cholesterol, Glucose
- Urinalysis : pH, Specific gravity, WBC, Protein, Bilirubin, Glucose, Urobilinogen, Ketone, Nitrite, Blood
- Collect concomitant drugs
- Collect adverse events

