### **11.7 Safety evaluation**

Check whether there is any adverse event through vital signs, hematological test, serum biochemical test and urinalysis immediately after surgery, at 1 week and 6 weeks after surgery.

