## **12. Predicted side effects and precautions for use**

### **12.1 Predicted side effects**

- 1) Side effects associated with general surgery : Abscess, cellulitis, wound, dermal necrosis, swelling, hematoma, cardiovascular disease, hypertension, ischemia, thrombus, embolism, hemorrhage, complications related to anesthesia, pulmonary complications, nerve/muscle damages, etc.
- 2) Side effects associated with the use of anti-adhesion product : Infection, allergic reaction, pain, and inflammatory reaction
- 3) Side effects associated with total thyroidectomy : Hypoparathyroidism, recurrent laryngeal nerve injury, hemorrhage, infection, superior laryngeal nerve paralysis, dyspnea, etc.

In the event of a predicted side effect, record the name and extent of the side effect as an adverse event in the Case Report Form according to the following criteria for mild, moderate and severe.

- Mild : A degree to which a subject can easily endure, without interfered with his/her normal daily life (or function) and with causing minimal discomfort
- Moderate : A degree to which it causes inconvenience to the extent that it significantly hinders the normal daily life (or function) of a subject
- Severe : A degree to which the normal daily life (or function) of a subject is impossible; a degree to which a subject is unable to continuously participate in the study; or a degree to which a subject needs to be treated or hospitalized

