## **15.4 Evaluation standard of safety**

In this clinical trial, all undesirable medical findings that develop symptoms that were not observed

before the application of the investigational product are classified as adverse events. The predicted side effects are also classified as adverse events, and the severity of adverse event is classified as mild, moderate, and severe.

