### 15.5 Safety evaluation method (statistical analysis method)

The analysis for the safety is ITT set. For all side effects reported during the study, determine the number of patients with the side effects, the rate and the number of occurrence by group. Analyze the incidence of adverse events between the test and control groups using the chi-square test (or Fisher's exact test).

Present descriptive statistics for adverse events by observation point and group. Among the results of hematological test, serum biochemical test and urinalysis, continuous data shall be presented as descriptive statistics (the number of subjects observed, mean, standard deviation, median, minimum and maximum), and categorical data as frequency and percentage. Since the occurrence of somatic signs is categorical data, it shall be presented as frequency and percentage. If necessary, these data can be compared and evaluated by applying statistical analysis (chi-square test, Fisher's exact test, unpaired t-test, paired t-test, etc.). The significance level of each statistical analysis is  $p < 0.05$ .

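### Hypoparathyroidism is a predicted adverse event reported by group, but the fixed serum panel has no calcium, so untested, untreated asymptomatic cases would be missed (minor, cheap to improve)

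*Protocol*

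**What the plan says.** Section 12.1 lists "Side effects associated with total thyroidectomy : Hypoparathyroidism, recurrent laryngeal nerve injury" among the predicted side effects, and section 15.4.1 repeats the list. Section 15.4 states that "The predicted side effects are also classified as adverse events", and section 15.5 asks the analyst to "determine the number of patients with the side effects, the rate and the number of occurrence by group".

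On detection, section 11.7 tells the investigator to "Check whether there is any adverse event through vital signs, hematological test, serum biochemical test and urinalysis". Section 11.1 spells out the serum part for Visit 1: "Serum biochemical test : sodium, Potassium, Chloride, Creatinine, BUN, ALT, AST,ALP, Total Bilirubin, Albumin, Total Protein, Total Cholesterol, Glucose". Visit 3 has the same list, and Visit 4 has it too, ending "Total Bilirubin, Albumin, Total Protein, Total Cholesterol, Glucose". The list is closed; nothing marks it as a set of examples.

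Footnote (3), printed under the schedule in the summary, in section 10.4 and in section 11, sets this rule: "if a subject is diagnosed with hypothyroidism or hypoparathyroidism through thyroid function test after thyroidectomy, the resulting adverse events should be followed up until". Its end point for that follow-up is each subject's final trial visit.

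**The concern.** The protocol expects hypoparathyroidism, gives it a follow-up rule of its own and counts it, but schedules no test that would show it when there are no symptoms. The one test named next to it is a thyroid function test. That test is in no schedule table or visit list and, in its ordinary meaning, does not assess the parathyroid glands. Whether an asymptomatic case is found then depends on what each hospital measures outside the protocol, which the document does not describe. At stake is how completely and evenly one named adverse event is ascertained for the safety tables.

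**Working it through.** No figure in the protocol is disputed. The check compares the text in several places and then counts what the change would cost.

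**1. Is the event one the trial means to count?** Yes. It is predicted (12.1, 15.4.1), classed as an adverse event (15.4) and reported by group (15.5).

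**2. Can a scheduled test show it without symptoms?**
- Serum panel (11.1): sodium, potassium, chloride, creatinine, BUN, ALT, AST, ALP, total bilirubin, albumin, total protein, total cholesterol, glucose. That is 13 analytes. Calcium, PTH and phosphate are absent.
- Schedule tables: the laboratory rows are urine β-HCG, haematology, serum biochemistry and urinalysis. None is for thyroid function, calcium or PTH.
- Serum draws in the schedule: Visits 1, 3 and 4, so 3. Calcium is measured at 0 of 3.

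**3. Which other routes lead into the adverse event record?**
- All adverse events are investigated at every postoperative visit (section 11), and subjects are told to report them (15.6.1).
- Section 15.1 includes abnormal laboratory results in the definition of an adverse event. Section 15.6.2 requires clinically significant laboratory abnormalities to be entered and does not restrict this to protocol tests. A low calcium found in routine care is therefore reportable even without symptoms.
- Concomitant drugs are collected at Visits 2, 3 and 4, so calcium or vitamin D started after surgery would be on record.

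What these routes leave uncovered is the asymptomatic case that no site tested for or treated in routine care.

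**4. Assays needed if calcium is added** (140 enrolled, section 8.3; 10% drop-out, section 8.4)
- Upper bound, no drop-out: 140 × 3 = 420, of which 140 × 2 = 280 are postoperative.
- Lower bound, with planned drop-out: 2 × 63 = 126 remain, so 140 − 126 = 14 leave. If all 14 leave before Visit 3: 140 + 126 × 2 = 140 + 252 = 392, of which 252 are postoperative.
- Screen failures add one assay each at Visit 1; their number is not given.
- Section 11.7 also mentions a check immediately after surgery. No schedule table or visit list has a serum draw at Visit 2, so none is counted here.

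**5. Number of cases affected.** The protocol gives neither a rate of hypoparathyroidism nor local testing practice, so this cannot be calculated.

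**The case against.** The case against has several parts.

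- **The event belongs to the operation.** Sections 12.1 and 15.4.1 keep side effects of the anti-adhesion product (infection, allergic reaction, pain, inflammatory reaction) apart from those of total thyroidectomy, and both arms have the same operation. This stands. A reader might infer that the device could disturb calcium; nothing in the protocol suggests it. The event is nevertheless counted by group whatever its cause.
- **Other capture routes exist.** This also stands and sets the limits of the point. It would be wrong to infer that hypoparathyroidism cannot be recorded, or that patients are left untreated: section 19.3 requires treatment of adverse events.
- **Footnote (3) is a follow-up rule.** Correct. A reader might take it as prescribing the wrong diagnostic test, but it prescribes none, and the loose wording changes no procedure and no follow-up time. Correcting it is editorial.
- **Uneven testing would fall on both arms.** Allocation is 1:1 in blocks, and the randomization code begins with an institution digit (11.3.1), which suggests allocation within site without stating it. Subjects and the independent evaluator are blinded. A reader might infer a biased comparison between arms; the protocol gives no ground for that.
- **The standard is selective.** The same list names laryngeal nerve injuries, for which no laryngoscopy is scheduled, and nothing requires a dedicated test for each predicted side effect. That is fair as a general rule. Calcium differs in one practical respect: serum is already drawn at three visits, and section 11.7 already names serum biochemistry as a means of finding adverse events.
- **Low calcium alone is not hypoparathyroidism.** This stands, and the remedy has to keep the two terms apart.

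**Conclusion.** The point holds as a minor, inexpensive improvement. Followed as written, the protocol has no scheduled test that would show an asymptomatic case of an adverse event that it predicts and reports by group. Cases that no site tested for or treated in routine care would be missed, and ascertainment may differ between the three sites.

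The omission itself is exact: calcium is 0 of 13 analytes at 0 of 3 serum draws. Its consequence has no derivable size. The effect is possible under-counting of a surgical complication; no arm bias, device effect or change to the primary endpoint analysis follows.

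The conclusion rests on two assumptions: that the analyte list is meant to be complete, as its wording indicates, and that a thyroid function test has its usual meaning, which the protocol does not define. The missing calcium does not depend on the second.

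**What to change.** - Add serum calcium to the serum biochemical panel at Visits 1, 3 and 4 in section 11.1, adjusted using the albumin already measured.
- Record clinically significant low values as hypocalcaemia under section 15.6.2.
- Reserve the term hypoparathyroidism for low calcium accompanied either by a low or inappropriately normal PTH from routine care, or by the investigator's documented diagnosis. PTH does not join the schedule.
- Reword footnote (3) in the summary, section 10.4 and section 11 so that only hypothyroidism is tied to the thyroid function test. Keep the last-visit limit on follow-up.

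The cost is 392 to 420 assays in enrolled subjects on serum already drawn, one more for each screen failure at Visit 1, and text changes in a few places. No visit, blood draw or follow-up time is added. The downside is an unknown number of additional laboratory adverse events for investigators to assess.
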